#### Measuring Instruments

To perform the effect evaluation of the planned intervention, several measuring instruments were chosen (see Table 4). Furthermore, the content of the process evaluation was defined.

**Table 4 T4:** Measuring instruments for the effect evaluation.

**Outcomes**	**Variables**	**Instruments**	**Descriptions**
Primary outcome	Mode, frequency, and duration of ACTS	Two valid self-report questions (37)	Behavior of cycling to school will be measured retrospectively for 5 weekdays: (a) Thinking about the last school week, how did you get to school/home from school each day?. Possible answers are walking, cycling, car, motorcycle, bus, underground/train/tram, or other. (b) Write beside the mode the journey start and end time.
Secondary outcome	Total MVPA in min per day	Accelerometers (ActiGraph wGT3X-BT)	On 7 consecutive days (38, 39), thigh-mounted (40) accelerometers with a sample rate of 30 Hz should be worn from waking up until going to bed except during water activities for a minimum of 8 h on a minimum of 3 weekdays and 1 weekend day (38, 39). Collected data will be downloaded using an epoch length of 1 s (38, 39). For wear time validation, the algorithm from Choi et al. will be applied (41). For data analysis, cut points from Hänggi et al. will be applied (42). For initialization and data processing of accelerometers, ActiLife will be used.
Moderators	Sociodemographic characteristics (5, 20)	Thirteen self-report questions	(a) Age/grade (b) Gender (c) Bicycle ownership/roadworthiness (d) Ability to cycle (e) Shortest distance from home to school by bicycle using Google Maps (43) (f) Zip code of the school (educational level, region) (g) Subjective socioeconomic status using the reliable “MacArthur Scale of subjective social status—youth version” (44) (h) Parents' restriction/allowance in terms of letting their child cycle to school (i) Family car ownership (45)
	Daily weather conditions (46)	Meteo Info	(a) Average rainfall in l/m^2^ (b) Average wind speed in km/h (c) Relative humidity in % (d) Temperature in °C (average, minimum, maximum)
Mediators	Regulatory styles of motivation types (amotivation, extrinsic motivation, intrinsic motivation)	“German behavioral regulation in cycling to and from school” (BR-CS) as self-report questionnaire based on the valid and reliable “Behavioral regulation in active commuting to and from school” (BR-ACS) questionnaire (47)	Twenty-three items with three or four items per regulatory style will be rated on a five-point Likert scale ranging from strongly disagree, disagree, neutral, agree to strongly agree.
	Satisfaction of the three BPNs autonomy, competence, and relatedness	“German basic psychological needs satisfaction in cycling to and from school scale” (BPNS-CS) as self-report questionnaire based on the valid and reliable “Basic psychological need satisfaction in active commuting to and from school scale” (BPNS-ACS) (48)	Twelve items with four items per need will be rated on a five-point Likert scale ranging from strongly disagree, disagree, neutral, agree to strongly agree.
	Cycling skills	Reliable practical cycling skills exam off-road (49)	Seven basic tasks representing essential situations in road traffic will be examined (i.e., slalom, slow driving, ascending/descending, driving in a narrow lane, turning left, driving an eight with one hand, braking between two lines).

*ACTS, active commuting to school; BPNs, basic psychological needs; MVPA, moderate-to-vigorous physical activity*.

To perform the pre- and post-measurement for the effect evaluation before and after the implementation of the intervention, participating classes will be divided into two small groups by the researcher and student assistants from TUM during two regular consecutive PE lessons with a total duration of 90 min. One group will answer the self-report questions in paper/pencil questionnaires, while the other group will perform a practical cycling skills exam off-road. Students who completed the questionnaire will be sent to the other group to complete the cycling skills exam and the other way around. At the end of the two regular consecutive PE lessons, accelerometers will be handed out and their handling will be explained to students (see Table 4). While wearing the accelerometers, weather conditions will be documented daily by a student assistant from TUM.

For the process evaluation during the implementation of the intervention, each art and PE teacher from each class that received the intervention will be asked to document in written form the dosage of their own intervention delivery (i.e., was the content of components implemented correctly), fidelity (i.e., what content of components was not implemented correctly and why), and any adaptions (i.e., what changes were made to the content of components during implementation). Thus, the dimension of the implementation of the intervention can be determined. Additionally, four willing students (two girls and two boys), four parents (two mothers and two fathers), and each art and PE teacher from each class that received the intervention will be asked in a structured online interview individually scheduled after the implementation of the intervention how they perceived the organization and content of the delivered intervention. They will also be asked to give feedback on their (dis)satisfaction regarding the intervention and to think about how it can be improved.

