#### Study Design

The main study is planned as a two-arm (i.e., intervention and control group (IG; CG)) three-level cluster (i.e., students in classrooms in schools) RCT (see Figure 4), whereby a simple randomization technique (i.e., flipping a coin) on school-level was chosen. For convenience, the pilot study will follow a quasi-experimental study design as a non-RCT. Directly before and after the implementation of the intervention, a pre- and post-measurement will take place as part of the effect evaluation. Furthermore, the process evaluation will take place during and after the implementation of the intervention. Based on the intraclass correlation coefficient (ICC) of 0.2 calculated for the variance of days per week students cycled to school between the three secondary schools in our concept mapping study (17), we assigned more than one secondary school to the IG and CG. No treatment will be delivered to the CG. In the main study, approximately 255 students belonging to five schools with two classes in grade(s) 7 and/or 8 will be in the IG and CG, respectively. However, approximately 150 students belonging to three schools will be in the IG and 100 students belonging to two schools in the CG when piloting the intervention.

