The decision to publish the detailed process of how our intervention was planned can be seen as a major strength as we demonstrate transparency of our structured procedure for other intervention planners. To the best of our knowledge, this is the first time that IM was used to plan an intervention aimed at the promotion of cycling to school. Our planned intervention has also several strengths: We chose the school setting for our intervention because it is regarded as ideal (50–53). According to the “Standing Conference of the Ministers of Education and Cultural Affairs” in Germany (54), the task to provide mobility and traffic education is assigned to schools, which we support with our planned intervention. Our intervention will contribute to closing the currently existing research gap by focusing on secondary schools where ACTS, especially cycling to school, is currently the least implemented activity (10) and generally, in an early development stage (9) with a lack of evidence for effectiveness in the majority of existing school-based interventions (11). We decided to focus on the promotion of cycling to school in winter (32) among the high-risk ACTS group of 12- to 15-year-olds (55) attending grade 7 or 8 (11) to expand the current state of research. As recommended, we chose a whole-of-school approach (56), a multi-level approach (21, 57), and a combination of objective as well as subjective measuring instruments to accurately assess the PA level during cycling (58). To prevent negative experiences on-road (e.g., accidents), we will first provide some theoretical and practical components off-road. Instead of choosing a top-down approach, we partly chose a participative approach to consider the opinion of the target group (i.e., students) and relevant stakeholders (i.e., parents and teachers), to address the local context appropriately, and to ensure the feasibility of the implementation of the intervention. The success of this approach will be controlled in the process evaluation. Furthermore, we will initiate collaborations (e.g., with the ADAC and police) free of charge and provide all necessary materials so that schools could continue the work beyond the duration of the intervention, which will ensure sustainability. Finally, we determined the appropriate sample size for an adequately powered effect evaluation, will control for potential mediators and moderators in our analysis (57) and will pilot the intervention. The purpose of piloting is to pre-test the effectiveness, acceptance, and feasibility of the intervention, as it will later be performed in the main study, in accordance with the planned organizational procedure and chosen measuring instruments for data collection described in this study protocol but by using a smaller sample size and a weaker, that is, quasi-experimental, study design.

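### Weather is recorded only in the accelerometer week, so as a moderator it is correctly timed for MVPA but comes from the wrong week for cycling days, the primary outcome

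*Protocol article*

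**What the plan says.** All references are to the protocol article.

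- **Primary outcome (Measuring Instruments, Table 4).** Travel mode is self-reported in retrospect for 5 weekdays: "Thinking about the last school week, how did you get to school/home from school each day". Journey start and end times are asked as well.
- **When it is asked (Measuring Instruments).** Each class is split during two consecutive PE lessons, 90 minutes in total: "One group will answer the self-report questions in paper/pencil questionnaires, while the other group will perform a practical cycling skills exam off-road". The groups then swap.
- **When the devices start (same section).** "At the end of the two regular consecutive PE lessons, accelerometers will be handed out and their handling will be explained to students". Table 4 sets wear at 7 consecutive days.
- **When weather is recorded (same section).** "While wearing the accelerometers, weather conditions will be documented daily by a student assistant from TUM".
- **Role of weather.** Table 4 places daily weather (rainfall, wind, humidity, temperature, from Meteo Info) under moderators. The Statistical Analysis section models cycling days and MVPA and then adds potential moderators, giving sociodemographic characteristics as its example.
- **Timing of waves (Study Design).** "Directly before and after the implementation of the intervention, a pre- and post-measurement will take place". The same session order applies at both.
- **Claim made (Discussion).** One listed strength is "a combination of objective as well as subjective measuring instruments to accurately assess the PA level during cycling (58".

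The article describes no weather record for the recalled week and no travel report for the wear week.

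**The concern.** A moderator of the primary outcome should describe the conditions under which that outcome arose. Here the weather offered to the cycling-days model is that of days after the cycling took place. If it is used there, the estimated moderation relates cycling in one week to rain, wind and temperature in another, and it will account for less of the variation in cycling than weather from the right days would.

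The plan itself treats conditions as important. The Program Implementation Plan section cites strong seasonal swings in cycling to school and runs the programme from fall to spring, through winter. Students measured in one session share one weather record, so the moderator varies only between sessions, and the main study has five schools per arm. There are few weather weeks over which a dating error could average out.

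The same ordering has a second consequence. The trips whose start and end times are reported were made before the device was worn, so activity during those trips cannot be read from the accelerometer. The Discussion's wording suggests that it can.

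A later analysis plan cannot supply a weather record that was not collected, so this is best settled in the data-collection procedure.

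**Working it through.** The plan states no figure on this point. Its one computed design figure, the sample size, uses neither weather nor MVPA: 2 × 4.1 × (1.960 + 0.842)² / 1.75² = 21.02, times 1 + (51 − 1) × 0.2 = 11, gives 231.2 against the stated 231. It reproduces and is unaffected.

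**Inputs.** Recall window: 5 school days before the session (Table 4). Questionnaire: during the session. Devices: from the end of the same session, for 7 consecutive days. Weather: the wear days only.

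**Set-up.** Number the days with Monday of the session week as 0, so a session on Monday to Friday is day w = 0, 1, 2, 3 or 4. The article does not say whether the session day counts as wear day 1, so take both cases: wear runs from s to s + 6, with s = w or s = w + 1. Take two readings of the recall question.

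**Reading A, the previous Monday to Friday.** Recalled days are −7 to −3. The earliest possible wear day is 0. Since −3 < 0, overlap is 0 of 5 for every w and both values of s.

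**Reading B, the last five school days before the session.** The latest recalled day is w − 1 (for a Monday session, the preceding Friday, day −3). The earliest wear day is w. Since w − 1 < w, overlap is again 0 of 5 throughout.

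| Reading | Shared days | Last recalled day to first weather day |
|---|---|---|
| A | 0 of 5 | 3 days (Monday session, same-day start: 0 − (−3)) to 8 days (Friday session, next-day start: 5 − (−3)) |
| B | 0 of 5 | 1 day (Tuesday to Friday, same-day start) to 4 days (Monday session, next-day start: 1 − (−3)) |

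**By outcome.**

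| Outcome | Days observed | Weather recorded on those days? |
|---|---|---|
| Cycling days (primary) | School week before the session | No |
| MVPA (secondary) | 7 days from the session | Yes |

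The order of questionnaire, hand-out and wear is the same before and after the intervention, so the result holds at both waves.

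**The case against.** The strongest reply is that nothing the plan sets out as an effect comparison depends on overlap. Cycling days and MVPA are each compared between arms, with the same procedure at the same wave in both. Weather is in the right week for one of the two modelled outcomes. The article never says outright that weather will enter the cycling-days model; that follows from Table 4 read with the Statistical Analysis section. All of this stands, and it makes the point a narrow one.

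Four stronger readings are tempting, and the documents do not support them.

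- **That the plan cannot show an effect on MVPA.** A reader might infer this from the non-overlapping weeks. The arm difference in MVPA needs no overlap, and the Statistical Analysis section specifies neither a path from cycling to MVPA nor an overlay of journey times on the trace. The link comes from the stated aim and the logic model. Adjacent weeks can still be related as two samples of usual behaviour, with some attenuation.
- **That the effect estimate for cycling is biased.** Zero shared days measures the timing, not an estimate. The cited seasonal contrasts compare seasons, not neighbouring weeks, and give no basis for a size.
- **That at post-measurement recall covers the last bicycle-train week and MVPA a week without the programme.** No session day is given. The train is voluntary and peer-run, and schools are meant to be able to continue the work, so the behaviour need not stop at week 20.
- **That the travel questions should simply move to device collection.** This would place the primary outcome in a week when students wear a device, with possible reactivity, and move post-intervention recall later. It would not reliably align the windows either. Under Reading A, with wear from the day after the session and collection on the next school day after wear, the unchanged question would cover 4, 3, 2, 1 or 5 wear days for Monday to Friday sessions. Only a Friday session gives full overlap.

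**Conclusion.** The point holds in a limited form. As scheduled, the weather recorded is correctly timed for MVPA and mistimed for cycling days: 0 of 5 recalled school days are covered at either wave, whichever weekday the session falls on and on either reading of the recall question. It affects weather as a moderator of the primary outcome, and any attempt to connect reported trips with measured activity in the same student. The between-arm comparisons of cycling days and of MVPA stand, and so does the sample size.

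The conclusion assumes that weather, being listed as a moderator, may be used in the cycling-days model, and that no weather record beyond the one described is kept. The size of any loss in the moderator analysis cannot be derived from the documents. The correction is nevertheless worth making, because it costs very little and the pilot is to use the same procedure and instruments.

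**What to change.** 1. **Weather for the recalled week.** At each wave and for each school, also obtain the same Meteo Info variables for the five recalled school days. Use those in the cycling-days model and keep wear-week weather for the MVPA model.
2. **Fix the dates.** State which five days the recall question denotes and record the session date, so that weather can be matched. If past days cannot be retrieved from the source (the article does not say), begin recording one school week earlier.
3. **Limit the claim.** Reword the Discussion so that it does not suggest activity is measured during the reported cycling trips. Describe any within-student association between cycling and MVPA as one between adjacent weeks.
4. **Optional.** Ask the travel questions again at device collection, worded for the wear days, as supportive information. This should not replace the primary-outcome recall.

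**Cost.** If all classes of a school are measured in the same week, item 1 adds 5 days × 2 waves × 10 schools = 100 daily weather records in the main study, and 5 × 2 × 5 = 50 in the pilot. Items 2 and 3 are changes of text. Item 4 takes a few minutes of class time. Items 1 and 2 should be in place before the pilot's first measurement.

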#### Data Handling, Storage, and Monitoring

Data will be collected using pseudonyms. Therefore, students will be instructed to create a six-digit ID code themselves to connect data throughout data collections and to ensure anonymity. Data collected for the effect evaluation will be entered in *SPSS*. Over a period of at least 10 years, data sets will be stored on central servers of TUM administered by the Leibniz–Rechenzentrum meeting the high standards of data safety in Germany. Only the researcher and manager of the ACTS project at TUM will get access to data sets, which means that anonymous data will not be made available for open access after the end of the study.

#### Statistical Analysis

To analyze the effectiveness of our intervention, a multiple group analysis considering the treatment factor (IG vs. CG) will be performed in a structural equation modeling using *R*. In this analysis, variances in the number of cycling days to school and MVPA due to belonging to different secondary schools will be considered in the following four levels: (a) repeated measurements for each student, (b) students, in which the repeated measurements are nested, (c) the class, to which each student belongs, and (d) the school, in which classes are nested. Subsequently, potential moderators (e.g., sociodemographic characteristics of the students) will be added to the model, and cycling to school will be regressed onto potential mediators (i.e., autonomy, competence, and relatedness) in levels (b–d). Furthermore, gender will be considered as a covariate in the analysis.

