#### Sample Size Determination

The optimal sample size for our chosen study design in the main study was calculated based on a formula by Rutterford et al. (34). This formula considers the confidence level (97.5%), power (80%), variance of days per week in cycling to school at the individual level [4.1 days (5)], our estimated clinically important difference in treatment means of days per week in cycling to school at the individual level (1.75 days), number of students per secondary school (based on the mean value in our concept mapping study: 51 students), and ICC of days per week students cycled to school at school level [0.2 days (17)]. According to this formula, the required number of students per intervention condition is 231. For the planned pilot study in the first instance, 10% of the main study's calculated sample size is recommended (35, 36) (i.e., 23 students per arm).

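### In the school-randomised main study, the pre-measurement is modelled as a repeated outcome and not used as a baseline; on the default reading this gives up some power if school-level pre-post correlation is below about 0.7

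*Protocol article*

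**What the plan says.** The Statistical Analysis section states that "a multiple group analysis considering the treatment factor (IG vs. CG) will be performed in a structural equation modeling". The first two of its four levels are "a) repeated measurements for each student, (b) students, in which the repeated measurements are nested"; classes and schools sit above them. Study Design says that "a pre- and post-measurement will take place as part of the effect evaluation", so the repeated measurements are one pre and one post value, and the pre value is part of the response.

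The same section gives roles to moderators and mediators and adds that "gender will be considered as a covariate in the analysis". It does not give the pre value of cycling days a role as a covariate. It does not say whether pre means are free or equal across arms, or which parameter is the treatment effect.

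In the main study "a simple randomization technique (i.e., flipping a coin) on school-level was chosen", whereas "the pilot study will follow a quasi-experimental study design as a non-RCT". The analysis text does not separate the two studies. Sample Size Determination plans on a "difference in treatment means of days per week" and makes no use of the pre value.

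**The concern.** In a multiple-group model, means are normally estimated within each group unless a constraint ties them. With pre and post both as outcomes and arm as the grouping variable, the natural contrast is the between-arm difference in pre-post change. In a randomised comparison the expected pre means are equal, so estimating them separately carries the noise of the pre-measurement into the effect. Using the pre value as a baseline removes that noise.

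At stake is power for the primary aim in a trial of ten schools, where data already being collected could be put to better use. Bias is not at stake.

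**Working it through.** **Inputs.** From Sample Size Determination: variance 4.1, difference 1.75 days, 51 students per school, ICC 0.2, power 80%, confidence level entered as 97.5%. From Study Design: five schools and about 255 students per arm. The pre-post correlation is not in the article and is varied here.

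**The plan's own figure.** Design effect = 1 + (51 − 1) × 0.2 = 11. Students per arm = 2 × (1.960 + 0.842)² × 4.1 / 1.75² × 11 = 21.02 × 11 = 231.2. The stated 231 reproduces, with 97.5% read as the quantile for a two-sided 5% test. The formula compares post means only. At 255 per arm it gives 83.7% power.

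**Which correlation matters.** Between-school variance is 0.2 × 4.1 = 0.82 and student variance is 0.8 × 4.1 = 3.28. A school mean has variance 0.82 + 3.28/51 = 0.82 + 0.064 = 0.884, of which 0.82/0.884 = 93% is between schools. The school-level correlation r therefore governs.

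**Large-sample variance.** Relative to a post-only comparison, a change comparison has factor 2(1 − r) and a baseline-adjusted one 1 − r². Their ratio is 2/(1 + r). Putting these factors into the plan's formula gives:

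| r | ratio | n per arm, change v adjusted | power at 255 per arm, change v adjusted |
|---|---|---|---|
| 0.3 | 1.54 | 324 v 211 | 70.1% v 87.0% |
| 0.5 | 1.33 | 232 v 174 | 83.7% v 92.5% |
| 0.7 | 1.18 | 139 v 118 | 96.7% v 98.5% |

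A change comparison falls below the plan's post-only basis only if r < 0.5.

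**With ten schools.** The formula ignores the few degrees of freedom and the need to estimate the baseline slope from ten schools. Simulated t tests on school means (8 df for change, 7 df for baseline adjustment), with r the correlation of school effects and an assumed student-level correlation of 0.5, give:

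| r | change | baseline-adjusted |
|---|---|---|
| 0.3 | 60% | 70% |
| 0.5 | 73% | 77–78% |
| 0.6 | 81% | 83% |
| 0.7 | 90% | 89% |
| 0.8 | 97% | 96% |

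A post-only t test has about 73% throughout. Defining r directly as the correlation of the observed school means shifts these figures by at most about two points (58% v 70% at 0.3; 92% v 90% at 0.7). The gain from adjustment is about 10 points at r = 0.3 and about 4 at 0.5. It is gone by about 0.7.

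**The case against.** The strongest objection is that the article never says that pre means are free or that the effect is a difference in change. A multiple-group structural equation model can hold pre means equal or regress post on pre. The sample size is stated for a difference in means, and such constraints often sit in an analysis plan, which is not shown here. This stands as a limit on the claim: the change comparison is a default reading. It does not remove the point, because the article does fix the pre value as a repeated outcome and does name its covariate.

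The second objection is that a low r is unsupported, and this stands too. A reader might infer from the winter timing that pre and post weeks correlate poorly. The Program Implementation Plan has the intervention run from fall to spring, and the Norwegian figures it cites are 52% in fall and 51% in spring. A seasonal shift common to all schools would not lower the between-school correlation. Recall noise in individual students is part of the student-level share, which makes up only about 7% of a school mean's variance. The correlates listed in the Logic Model of the Problem, such as distance, region and educational level, are largely stable over five months.

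Third, the simulation has limits. It covers school-mean tests, not the full four-level model, and the equal-means constraint was not simulated. At r = 0.3 a post-only test (73%) slightly beats school-level baseline adjustment (70%), because the slope costs a degree of freedom.

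**Conclusion.** The point holds in conditional form. As written, the pre value is an outcome and not a baseline. On the default reading, the main study would compare change and leave the school randomisation unused. Relative to baseline adjustment, the loss is about 10 points of power at r = 0.3, 4 to 5 at 0.5 and 2 at 0.6, with none from about 0.7. These figures rest on the plan's own variance, ICC, effect and school size, on an assumed r, and on school-mean tests.

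Two stronger readings are tempting. One is that the plan has committed to change scores and the trial is therefore underpowered. The article does not state that contrast, its 231 reproduces, and that figure is undercut only if r is below 0.5, for which the article gives no evidence. The other is that the planned analysis is biased. Under randomisation a comparison of change is valid, so this is a matter of efficiency. Free pre means are also appropriate in the pilot, where allocation is not random.

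**What to change.** State in the Statistical Analysis section that, for the randomised main study, the treatment effect on the primary outcome is the IG minus CG difference in post cycling days. Estimate it either with the pre means constrained equal across arms in the multiple-group model, or with the pre value as a covariate. If a covariate is used, enter it at school as well as student level, since the school level governs precision. State separately that equal pre means are not imposed in the non-randomised pilot.

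The change needs one constraint or covariate and no new data. It costs one degree of freedom, which in a ten-school analysis is about 1 to 2 points of power if r is 0.7 to 0.8. If equal pre means or a baseline covariate was already intended, one sentence saying so settles the point.
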